## Methods

### Ethics

Approval was obtained from the ethics committee of the Faculty of Social & Behavioural Sciences of Utrecht University on 26 September 2025. The ethics committee will be informed of all significant study amendments. The study is registered at the Overview of Medical Research in the Netherlands [54] (NL-OMON58273) on 4 December 2025. Results will be reported using SPENT guidelines [55].

### Study design

A single case observational design (SCOD) will be used to examine treatment effects [51]. More specifically, an A/B-phase design is used. Within this design, phases A and B may respectively represent the baseline and intervention phases – or all measurements before and after the expected start of the treatment effect (in case of interventions with delayed or lagged treatment effects) [51]. In our study, we expect that the treatment effect will start after the first module (i.e., three weeks after the start of the intervention). Therefore, we will label all observations collected before and during the first module as part of Phase A, and all observations after the first module as part of Phase B. This means that Phase A consists of 6 weeks (3 weeks baseline plus 3 weeks module 1) and Phase B consists of 9 weeks (modules 2, 3, and 4). The outcome variables of interest will be monitored through repeated measurements three times per week in both phases [51]. Although the current study design does entail an experimental intervention, we refer to the design as ‘observational’ because the start of the intervention cannot be randomized across participants – a procedure that usually increases the internal validity of the single case design [56]. The start cannot be randomized for practical reasons at the institutes’ organizational level and for ethical reasons (e.g., potentially postponing the start of training for some participants). In such cases, it has been suggested to observe the start of the intervention as a ‘natural event’ and analyze the data with statistical methods that treat the data accordingly [51]. All participants in one group will start the training at the same time, three weeks after completing the baseline questionnaire. The study ends with a follow-up questionnaire after the last training session has ended. There is no additional follow-up phase with repeated measurements incorporated.

### Participants and recruitment

In total, 30 participants will be included in the study. Youth who seek help for depressive symptoms, anxiety symptoms and/or stress that are advised to follow the STARr training are eligible to participate. To be eligible to participate in this study, a participant needs to be registered for the STARr training at one of the two participating mental health organizations and be between 12 and 20 years old. When a participant has acute and severe suicidal thoughts and/or intentions (a score of 2 on the Children’s Depression Inventory-2 (CDI-2) item ‘a desire to kill oneself, if given the chance’ on the CDI-2 [57] in combination with a total score of 12 or higher on the suicide items of the Questionnaire about suicide and self-harm [58], the trainer will be notified. The trainer will follow the organization’s protocol regarding suicidality and will decide whether the participant can continue the training.

Participants will be recruited through the two mental health organizations. Youth who register at one of the two organizations for a STARr intervention will receive information about the study and will be invited to participate. Youth will receive an information letter and the informed consent form. If youth are aged between 12 and 16 years old, their parents will also receive an information letter and an informed consent form. Youth have two weeks to decide whether they want to participate, and they can provide informed consent online through Qualtrics. Parents of youth aged between 12 and 16 years will also have to provide consent for their child. If youth do not want to participate, they will still receive the STARr training. They can also withdraw from the study at any time without explanation and continue the STARr training. When a participant withdraws from the STARr training and the study, they will receive an exit questionnaire that includes the same items as the long questionnaires along with an additional open-ended question inviting them to elaborate on their reasons for discontinuing the STARr training.

### Sample size and power calculation

We used a power calculation application for single-case designs [59] to calculate the expected power when utilizing a permutation distancing test with a total of 30 participants who complete the study. Participants will receive a total of 45 repeated measurements, of which 18 belong to Phase A and 27 to Phase B. With a mean difference of 1.5 units (small treatment effect) between phases A and B (SD phase A = 3 and SD phase B = 3), and a missing percentage of 20% and autocorrelation level of 0.2, the power would be 79%. It is important to note that this is the calculated overall power is calculated for the group. The power per individual could be lower or higher, depending on, e.g. the percentage of missing observations and the level of autocorrelation between observations.

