This study faces several challenges. First, for the inclusion of participants, we are dependent on the registrations of participants at the organizations. We are only able to ask youth to participate in the study after they have registered for the training at one of the two organizations. Further, a minimum of 80% of completed questionnaires from 30 participants is needed to have sufficient power for all planned analyses, while we are aware that dropout from CBT or studies into CBT is prevalent [98, 99]. To reduce drop-out, youth are motivated to complete questionnaires by compensating them with 90 euros when they complete all questionnaires. In addition, there is a strong collaboration between researchers and trainers, so when participants do not complete the questionnaires, trainers can send out reminders immediately. Also, trainers are instructed to motivate participants to complete questionnaires during the training. A last challenge relates to incorporating personalization in group training. Because participants may have diverse preferences and needs, individual training seems a better fit. For example, regarding the sequence of modules, not all participants will receive their preferred sequence of modules. Nevertheless, the STARr training is adapted in such a way that we expect it will meet the needs of a broad group of adolescents regarding educational level, cultural background, sexual orientation, and gender. Also, we want to mimic clinical practice as much as possible. Preventative interventions are often offered in group format to reduce costs. Therefore, we decided to offer the training in a group format and using the majority of preferences to determine the most appropriate sequence.

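### The 79% power is for 30 completers but only 30 will be included, and the Discussion extends it to all planned analyses although only the A-B test was powered

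*Protocol article*

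**What the plan says.** All references are to the protocol article.

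- **Sample size and power calculation.** Power is computed for "a permutation distancing test with a total of 30 participants who complete the study". Each participant has "a total of 45 repeated measurements, of which 18 belong to Phase A and 27 to Phase B". The assumed effect is given as "With a mean difference of 1.5 units (small treatment effect) between phases A and B", with "SD phase A = 3 and SD phase B = 3". The result is stated as "a missing percentage of 20% and autocorrelation level of 0.2, the power would be 79" per cent, and the section says that it refers to the group, not to individuals.
- **Participants and recruitment.** "In total, 30 participants will be included in the study". The Abstract gives the same number as an aim. Participants may withdraw at any time.
- **Discussion.** "a minimum of 80% of completed questionnaires from 30 participants is needed to have sufficient power for all planned analyses". The same sentence acknowledges that dropout from CBT and from CBT studies is common, and retention measures follow.
- **Statistical analyses.** Besides the A-B comparison, the plan has three sequence preferences and three treatment characteristics as predictors of change, gender and age in interaction with module sequence, and four mediators.
- **Intervention and Procedure.** Training is given in groups of six to eight, and each group receives a single module sequence.

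**The concern.** The number of completers in the power calculation equals the number to be included. The 79% therefore makes no allowance for participants who leave, and it already lies just under 80%. The 20% missingness does not fill the gap: it is a share of observations, applied to people who are assumed to complete.

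The Discussion then attaches that sample to all planned analyses. The only calculation shown is for the A-B mean difference, which draws on up to 45 measurements per person. A person-level predictor has at most 30 independent units, and module sequence has only as many as there are training groups.

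One objective is to find which of three preferences best predicts improvement. If the Discussion's sentence stands, a null result there, or for a moderator, could be taken as adequately powered evidence of no effect.

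**Working it through.** **1. Trying to reproduce the 79%.** Inputs from Sample size and power calculation: 18 and 27 observations, difference 1.5, SD 3, 20% missing, autocorrelation 0.2, 30 completers. Alpha, sidedness and the rule for combining participants are not stated; 0.05 is assumed.

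- One participant, ignoring autocorrelation: 18 × 0.8 = 14.4 and 27 × 0.8 = 21.6 observations. SE = 3 × √(1/14.4 + 1/21.6) = 1.02, and 1.5/1.02 = 1.47. Power is Φ(1.47 − 1.96) = 31% two-sided, or Φ(1.47 − 1.645) = 43% one-sided.
- Group mean of 30, same effect in everyone: the autocorrelation inflates the variance by about (1 + 0.2)/(1 − 0.2) = 1.5, so SE per person = 1.02 × √1.5 = 1.25. Then z = (1.5/1.25) × √30 = 6.57, and power is about 100%.
- Group mean of 30 with a between-person SD of the effect of 2.7 (not in the document): z = 1.5 × √30 / √(1.25² + 2.7²) = 2.76, and power is Φ(0.80) = 79%.
- One-sample test with d = 1.5/3 = 0.5 and n = 30: Φ(0.5 × √30 − 1.96) = 78%. This comes close, but it uses none of the repeated-measures inputs.

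The 79% is therefore not reproduced uniquely.

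**2. Effect of losing participants.** Take 79% as given at 30, two-sided 0.05: z = 1.96 + 0.806 = 2.766. Scaled power is Φ(2.766 × √(n/30) − 1.96). The dropout rates are assumptions.

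| Completers | Dropout | Scaled power |
|---|---|---|
| 27 | 10% | 75% |
| 24 | 20% | 70% |
| 21 | 30% | 64% |

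The range depends on how much the effect varies between people. With 21 completers, the group-mean formula in step 1 gives about 100% for a between-person SD of 0, 99% for 1, 83% for 2 and 64% for 2.7.

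**3. Why the 20% does not cover leavers.** The full set is 30 × 45 = 1,350 questionnaires. If six people left at the start of Phase B, 6 × 27 = 162 would be lost, which is 12%. An 80% completion threshold, read as a pooled figure, would still be met with only 24 A-B contrasts.

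**4. The other analyses at n = 30, two-sided 0.05, before any dropout.**

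- One person-level predictor (Fisher z): power = Φ(atanh(r) × √27 − 1.96). At r = 0.3 this is Φ(1.61 − 1.96) = 36%. For 80%, r = tanh((1.96 + 0.842)/√27) = 0.49. With 24 completers the figures are 29% and 0.55.
- Three predictors jointly at f² = 0.15 (noncentral F, 3 and 26 df, λ = 0.15 × 30 = 4.5): 35%.
- Two subgroups of 15 that differ by 0.5 SD, the standardized size used in the plan's own calculation (noncentral t): 26%.
- Module sequence: 30/8 = 3.75 to 30/6 = 5, so roughly four to five groups if all members take part in the study. Mediation and moderation analyses itself concedes that moderators can be assessed only if several sequences are delivered.

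**The case against.** Several points on the other side are sound.

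- **The loss of power is not established.** A reader might infer that 79% is attainable only with zero dropout, or that the primary test is underpowered. The document does not support either. If the effect is similar across participants, group power stays near 100% even with 21 completers. What stands is that the stated figure is conditional on 30 completers and has no attrition allowance.
- **Not every leaver loses all of Phase B.** It runs over nine weeks and three modules, and the test uses whatever observations exist. Someone who leaves in the third or fourth module still contributes a contrast. Missingness below 20% among the others would also offset some loss. Only those who leave before or early in Phase B contribute none.
- **The Discussion states a requirement and lists it as a challenge.** It does not promise that power is assured, and it describes retention measures. That is fair, but the sentence still says that 30 participants with 80% of questionnaires would suffice for every analysis.
- **A flat statement that power is inadequate for the other analyses goes too far.** In a person-level simulation with n = 30, mediation reaches 79% power when both paths are 0.59, against 29% when both are 0.39. The planned mediation is multilevel and the mediators are also measured three times a week, so a model using those data could do better than these figures.
- **Exploratory labels often sit in the analysis plan, which is not shown.** Their absence is not the point; the breadth of the sentence in the Discussion is.

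**Conclusion.** The concern holds on two points of text. The 79% applies to 30 completers while only 30 are to be included, with no allowance for the dropout that the Discussion expects. The extension to all planned analyses rests on a calculation for the A-B permutation distancing test alone. It is unsupported, and untrue unless effects are large: 36% power for a single predictor at r = 0.3, and 80% only at |r| of about 0.49, with n = 30 and two-sided 0.05.

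The scaled values of 75%, 70% and 64% are illustrative. They assume that 79% is correct, that power scales with √n, and the dropout rates shown. No arithmetic error is demonstrated, and the primary test itself is not shown to be inadequate. This should be fixed, but it does not undermine the trial's main comparison.

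**What to change.** 1. In Sample size and power calculation, keep 30 as the number included. Rerun the same power application for a stated range of expected completers, for example 27, 24 and 21, labelled as assumptions. Report those results in place of the single 79%, with alpha, sidedness and the rule for combining participants. Use the application's output, not the scaled values above.
2. In the Discussion, limit the power statement to the primary A-B contrast. Describe the predictor, moderator and mediator analyses as exploratory, so that null results are not read as adequately powered evidence of no effect.

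The cost is text changes, a rerun of the application and a less favourable stated power. Making 30 the number of completers instead would not be a text-only change: by N = 30/(1 − d), it means enrolling 34, 38 or 43 at an assumed dropout of 10%, 20% or 30%.

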### Intervention

STARr is a group training and takes place in groups of six to eight participants. The STARr-intervention consists of four modules that are based on the core elements of CBT for depression: problem solving (Solve), cognitive restructuring (Think), behavioral activation (Act&do), and relaxation (Relax). These elements are theoretically well-founded and incorporated in most CBT interventions for young people with depressive symptoms [17, 60, 61]. Participants receive a combination of these four modules in weekly sessions (3 sessions per module), and the program’s total duration is 12 weeks [28]. Participants receive a workbook that contains (homework) exercises for each module.

The adapted version of the STARr training (STARr2.0) is grounded in the same theoretical framework as the original STARr training. Accordingly, it remains a modular, preventative group training consisting of 12 one-hour sessions targeting youth aged 12 to 20 experiencing depressive symptoms and/or (comorbid) stress and anxiety. To enhance accessibility and inclusivity, several adaptations were made: workbook texts were shortened and rewritten at B1 level, images and more active exercises were added to support understanding, and more diverse examples reflecting educational, cultural, sexual, and gender diversity were included. The adapted training that will be investigated will be delivered in groups of six to eight participants.

### Procedure

The STARr training will be provided by two mental health organizations in the Netherlands. Professionals from both organizations were trained by two researchers/psychologists from the research team who developed the STARr training. The trained professionals will deliver the training. See Fig. 1 for an overview of the procedure and data collection points.

**Fig. 1 Fig1:**
[figure not shown]
Procedure and data collection points

Participants will receive one of the four module sequences assessed in the previous STARr study, which has been shown to be associated with a significant reduction in depressive symptoms. The following sequences of modules were assessed in the previous STARr study: Think-Act-Relax-Solve (1), Act-Think-Relax-Solve (2), Solve-Act-Think-Relax (3), and Relax-Solve-Act-Think (4). The sequence will be based on three factors: youth’s preference, trainer’s preference, and a data-driven prediction. During the intake, the trainer explains the content of the four modules to the participant and asks the adolescent which sequence of modules (options 1, 2, 3, or 4) would fit best based on the participant’s needs and struggles (participant’s preference). Particular attention is given to the first preferred module (problem solving, cognitive restructuring, activation or relaxation). Next, trainers indicate to the researcher their preferred module order for each participant, based on the intake and the nature of the participant’s needs and symptoms (trainers’ preference). Finally, an algorithm determines the most suitable module sequence per participant (PAI) [22] (data-driven prediction). This data-driven prediction uses an algorithm that is based on data from the previous STARr study [26]. Personalized Advantage Indexes (PAI) were calculated using a random forest algorithm [22, 62]. Using the random forest algorithm, the PAI-scores are calculated for participants of the current study using the baseline questionnaire data. The variables included in the algorithm are gender (boy/girl), age, Dutch/non-Dutch ethnicity, and variables regarding depressive symptoms, comorbidity, problem-solving approaches, negative cognitive errors, behavioral activation, and stress.

The two preferences (participant and trainer) and the prediction (data-driven) of all participants in one training group are then summed up, and the most frequently selected sequence is delivered in that group. These three preferences are subsequently used as predictors for the study outcomes.

### Measures

The following measures are included in the study. Table 1 provides an overview of the timing of each measurement.

**Table 1 Tab1:** Overview of assessments

Type of variable	Domain/ Concept	Instrument		Assessment					
			Items	A	T	t_0_	T_w_	T_m_	T_*p*_
Primary outcome	Depressive symptoms	CDI-2	28	x		x		x	x
		CDI-2 2 item	2				x		
Secondary outcome	Depressive symptoms	NRS for core symptoms of depression	3	x		x		x	x
	Anxiety symptoms	NRS 2 items	2				x		
		SCARED-5 + items social anxiety	13	x		x		x	x
		SCARED 2 item	2	x			x		
	Top three problems	TP measure	3	x		x			x
	Suicidal ideation (if score 2 on item 8 CDI-2)	VOZZ suicide items	8/4	x		x		x	x
	Comorbidity	BPM	19	x		x		x	x
	Individual societal impact questionnaire	ISIQ	10	x		x		x	x
Mediators	Negative cognitive errors	CNCEQ-R	16	x		x		x	x
		CNCEQ-r 2 items	2				x		
	Behavioural activation	BADS	25	x		x		x	x
		BADS 2-item	2				x		
	Problem solving skills	SPSI-R	10	x		x		x	x
		SPSI-R 2 items	2				x		
	Relaxation	PSS-10	10	x		x		x	x
		PSS-10 2 items	2				x		
		NRS for relaxation	1	x		x		x	x
Moderators	Demographics adolescent			x		x			
Treatment characteristics	Current and previous treatment	VEHI	6	x		x			x
	Expectancy of treatment	PETS	7	x		x			
	Therapeutic alliance	TASC-r	12	x				x	x
	Satisfaction treatment	SSS	3	x				x	
	Youth’s motivation for treatment	MYTS	8	x		x		x	x
	Module questionnaire		5	x				x	x
	Drop-out / amount completed sessions				x				
	Treatment integrity				x			x	

*Abbreviations*: *A* adolescent, *FV* full-length version, *NRS* Numerical Rating Scale, *SV* short version, *T* therapist, *t*_*0*_ baseline assessment, *t*_*w*_weekly assessments (three times a week), *t*_*m*_ post-module assessment, *t*_*p*_ post-intervention assessment

*Depressive symptoms* are assessed using the Children’s Depression Inventory-2 (CDI-2) [57]. The CDI-2 consists of 28 items, and response options are rated on a 3-point scale. A higher score indicates more severe symptoms. The CDI-2 has demonstrated good reliability and validity [57]. The Cronbach’s alpha in the previous STARr study varied between 0.86 and 0.90 [26].

*Anxiety* is assessed with the Screen for Child Anxiety Related Emotional Disorders (SCARED)-5 [63, 64] and eight additional items from the social anxiety subscale of the SCARED-71 questionnaire [65]. These 13 items are rated on a 3-point scale ranging from “not true or hardly ever true” to “very true or often true”. The SCARED has demonstrated good reliability and validity [65].

*Individual and societal functioning* is assessed with the Individual and Societal Impact Questionnaire (ISIQ) [66]. The questionnaire includes questions about physical health, mental health, personal hygiene, school and work, friendships, romantic relationships, family, daily activities, independence and leisure time. Items are rated on a 6-point Likert scale ranging from “none” to “a lot”. The ISIQ showed good reliability [67].

*Suicide risk* will be assessed with eight items of the suicide and self-harm questionnaire (VOZZ) [58]. These items measure past and present suicidality. Response options are rated on a 5-point scale. A higher score indicates more severe symptoms. The VOZZ has demonstrated good reliability and validity [58].

*Comorbidity* is assessed with the Brief Problem Monitor (BPM) [68].

The BPM consists of 18 items divided into three subscales: internalizing, externalizing and attention problems. Response options are rated on a 3-point scale from “not true” to “very true”. The BPM has demonstrated good reliability and validity [68].

*Problem-solving approaches* in daily life will be assessed with the short form of The Social Problem Solving Inventory-Revised (SPSI-R) [69]. This measure consists of 10 items and includes five subscales: positive problem orientation, negative problem orientation, rational problem solving, impulsivity/carelessness style, and avoidance style. Response options are rated on a 5-point Likert scale ranging from “not at all true” to “extremely true of me”. The SPSI-R showed good reliability and validity [70].

*Negative cognitive errors* will be assessed with the Children’s Negative Cognitive Errors Questionnaire – Revised (CNCEQ-R) [71]. This questionnaire measures five negative cognitive errors: underestimation of the ability to cope, personalizing without mind-reading, mind-reading, selective abstraction, and overgeneralizing. Response options are rated on a 5-point Likert scale ranging from “not at all like I would think” to “almost exactly like I would think”. The CNCEQ-R showed moderate to good reliability and validity [71, 72].

*Behavioral activation* will be assessed with the Behavioral Activation for Depression Scale (BADS) [73]. The BADS consists of four subscales: activation, avoidance/rumination, work/school impairment, and social impairment. Response options are rated on a 7-point Likert scale ranging from “not at all” to “completely”. The BADS demonstrated acceptable to good reliability and validity [73–75].

*Stress* will be assessed with The Perceived Stress Scale (PSS-10) [76, 77]. Response options are rated on a 5-point scale ranging from “never” to “very often”. The PSS-10 has demonstrated acceptable reliability and validity [78].

